### 2.2. Study Population

Consecutive patients with clinical suspicion of PCa—defined as an elevated prostate-specific antigen (PSA) level > 4 ng/mL, an abnormal digital rectal examination, or both, without prior prostate biopsy—will be recruited from outpatient clinics. Eligibility criteria, key contraindications, and the imaging workflow, including acquisition of the TDD sequence, are summarized in Figure 1. All participants will provide written informed consent prior to enrollment.

According to the local standard-of-care diagnostic pathway, men with clinical suspicion of PCa undergo mpMRI (including T2-weighted (T2W), diffusion-weighted (DWI), and dynamic contrast-enhanced (DCE) sequences). The dominant and any additional PI-RADS ≥ 3 lesions are scored by a senior radiologist with at least 10 years of experience using the PI-RADS v2.1 system:PI-RADS 1: Very low (clinically significant cancer highly unlikely).PI-RADS 2: Low (clinically significant cancer unlikely).PI-RADS 3: Intermediate (equivocal).PI-RADS 4: High (clinically significant cancer likely).PI-RADS 5: Very high (clinically significant cancer highly likely).

Patients with PI-RADS 1–2 findings are not offered biopsy, while those with PI-RADS 3–5 lesions undergo prostate biopsy as per standard of care, following the Ginsburg protocol [36]. Biopsy results are interpreted according to the EAU–EANM–ESTRO–ESUR–ISUP–SIOG guidelines [2] and serve as the diagnostic reference standard for this study.

For the purpose of this study, all enrolled patients will undergo an additional 4.5-minute TDD sequence during the same visit as the standard mpMRI. All image data will be exported to a dedicated database. Only standard-of-care mpMRI sequences will be stored in the institutional Picture Archiving and Communication Systems (PACS) for clinical use. We will report baseline clinical and imaging characteristics (e.g., age, PSA, PSA density, prostate volume, prior MRI findings, and scanner/protocol variables) for the full cohort and, where applicable, by analysis split (training/validation/test) and by PI-RADS category.

### 2.3. Input-Data Eligibility and Non-Evaluable Examinations

For a case to be evaluable for the primary analysis, mpMRI must include diagnostically adequate T2W, DWI (including high b-value), and DCE, plus the additional TDD sequence acquired per protocol with complete prostate coverage. An examination will be classified as non-evaluable for the primary analysis if any of the following prespecified conditions occur: (one) the magnetic resonance imaging examination is incomplete or prematurely terminated; (two) time-dependent diffusion acquisition fails or is not acquired according to the prespecified protocol; (three) severe motion, susceptibility, or other artifacts prevent reliable region of interest definition or parameter extraction for the index lesion; (four) prostate gland or lesion segmentation fails despite prespecified fallback procedures; (five) biopsy verification for the PI-RADS category 3–4 primary analysis cohort is not obtained within the prespecified verification window due to patient refusal, contraindication, loss to follow up, or clinical decision changes. Non-evaluable cases will be reported with reasons and accounted for in the participant flow and sensitivity analyses.

### 2.4. Prostate Magnetic Resonance Imaging Data Acquisition and Fitting for Determination of Microstructural Parameters

Multiparametric MRI will be performed on a 3.0 T scanner with the participant in the supine position using a pelvic phased-array coil with or without an endorectal coil. Standard mpMRI sequences (T2W, DWI, and DCE) will be acquired following consensus guidelines [37].

An additional TDD sequence will be acquired following the protocol proposed by Wu et al. [27]. This protocol uses oscillating gradient spin-echo frequencies of 33 Hz (effective diffusion time = 7.5 ms, two cycles, b = 300 and 600 s/mm^2^) and 17 Hz (effective diffusion time = 15 ms, one cycle, b = 400, 800, and 1200 s/mm^2^) [27], and pulsed gradient spin-echo sequences at diffusion duration and separation of 10 and 30 msec, respectively (effective diffusion time = 26.7 ms, b = 400, 800, and 1200 s/mm^2^), with a maximum gradient of 45 mT/m and maximum slew rate of 200 mT/m/msec [27].

Diffusion data will be analyzed with a two-compartment model with impermeable spheres [26], fitted by non-linear least squares optimization in Matlab (Version R2025b) (MathWorks). To avoid local minima, the fitting will be repeated 20 times with randomized initialization. The signal model is given by the following:(1)$$S=v_{in}\cdot S_{in}\cdot \left(1-v_{in}\right)\cdot e^{-b\cdot D_{ex}}$$
where $v_{in}$ is the intracellular volume fraction; $S_{in}$ is the intracellular signal (as defined by Jiang et al. [26] for trapezoidal OGSE encoding [23]); ***b*** is the diffusion-weighting factor; and ***D_ex_*** is the extracellular diffusivity [19,26]. The Matlab routine provided by Jiang et al. [38] will be used.

### 2.5. Artificial Intelligence-Based Automatic Delineation of the Prostate Gland Zones

This study aims to develop and validate an AI-based framework for the automatic delineation of prostate zones and suspicious lesions, enabling accurate three-dimensional quantification of microstructural parameters for the prediction of csPCa.

#### 2.5.1. Training Dataset and Human-in-the-Loop Strategy

DL-based segmentation requires annotated data. We will begin with the publicly available PI-CAI dataset [39] and its annotations [40]. The relevance of this dataset is that it comprises mpMRI examinations collected for addressing challenges around prostate lesion detection and classification. It provides T2W, DWI, and apparent diffusion coefficient (ADC) images acquired on Siemens scanners, along with lesion annotations and clinical significance labels (biopsy-confirmed Gleason Grade Group) for a subset of patients. For local patient data, a Human-in-the-Loop strategy will be implemented: batches of automatic segmentations from a “no new U-Net” nnU-Net trained on the public dataset will be iteratively corrected by expert radiologists [41,42]. Corrected masks are added to the training set, and the model is retrained until convergence, defined by radiologist-established criteria. Model performance will be evaluated on an unseen test set using the Dice coefficient or more sophisticated Dice variants measurements.

#### 2.5.2. Segmentation Models

Automatic segmentation will primarily rely on nnU-Net [42], a self-configuring deep learning framework that automatically adapts pre-processing, network architecture, training schedules, and post-processing to the characteristics of each dataset. This approach is based on the U-Net architecture, employing a contracting path to capture contextual information and an expanding path to delineate regions of interest with high precision. For additional flexibility and integration of custom architectures, we will also leverage the Medical Open Network for Artificial Intelligence (MONAI) framework [43]. MONAI (v1.5.1) is a PyTorch-based open-source framework (PyTorch v2.9.1) that provides medical imaging-specific transforms, model architectures, and utilities to streamline the development and deployment of clinical AI models. Together, nnU-Net and MONAI establish a robust, state-of-the-art segmentation pipeline that is reproducible and adaptable to diverse imaging datasets. The primary segmentation metric will be the Dice coefficient. All models will be evaluated on the same prespecified, patient-level held-out test set—locked prior to training and never used for model development—hyperparameter tuning, or early stopping to ensure fair, like-for-like comparisons.

In addition to these baselines, we will consider foundation models such as the Medical Segment Anything Model (MedSAM), which leverages large-scale pre-training for cross-domain adaptability and can be adapted for automatic use via lightweight fine-tuning or prompt generation [44]. MedSAM is trained on over 1.5 million annotated medical images and significantly improves segmentation performance across a wide variety of anatomical structures and imaging modalities. We will also evaluate ProGNet [45], a U-Net derivative optimized for automatic prostate segmentation. ProGNet has been retrospectively validated on 905 patients and prospectively tested, achieving mean Dice coefficients of 0.92 and 0.93, respectively, while reducing segmentation time from >10 min manually to ~35 s per case. Its code is publicly available for reproducibility and external validation [45,46].

#### 2.5.3. Integration with Microstructural Analysis

Automatic segmentations will define all regions of interest (ROIs) for TDD-derived microstructural parameter extraction. Combined with biopsy results, these metrics will be used to train the PROS-TD-AI DL model for lesion-level risk prediction, aiming to improve reproducibility, reduce inter-observer variability, and support clinical decision-making.

#### 2.5.4. Model Governance

Versioning: All AI components (segmentation, parameter estimation, and classification) will be version-controlled (code, pre-processing, and trained weights). The final selected model will be locked (frozen parameters) prior to final evaluation, and any subsequent modifications will be released as a new version and evaluated separately.Bias Mitigation: To mitigate bias and leakage, data splitting is performed at the patient level only, with stratification by csPCa status; all pre-processing, feature selection, calibration, and threshold tuning will occur within training folds. We will report performance stratified by clinically relevant subgroups (e.g., peripheral vs. transition zone; PI-RADS category) to assess heterogeneity.Explainability: The system will output clinician-facing results, including ROI overlays and lesion-level probability scores. For model transparency, we will report feature importance/attribution (e.g., permutation importance or SHAP for tree-based models) and calibration summaries, while emphasizing that explainability outputs are supportive and not used for ground-truth determination.Monitoring: We will prospectively log non-evaluable cases and failure modes (e.g., missing sequences, motion/artifacts, and segmentation/fit failure) and report their frequency and impact on performance. During this observational study, PROS-TD-AI outputs will not influence clinical management.

### 2.6. Radiological Imaging Analysis

All standard mpMRI examinations (excluding the TDD sequence) will be interpreted according to PI-RADS v2.1 by radiologists through PACS. After signing the report, the radiologist will segment the index lesion and any additional PI-RADS 3-4 lesions within one month, blinded to biopsy results. These segmented regions will define the ROIs for extracting microstructural parameters from co-registered TDD images. TDD-derived maps will not be displayed during lesion contouring.

Microstructural parameters—including intracellular volume fraction (v***_in_***), cell diameter (***d***), extracellular diffusivity (***D_ex_***), and cellularity index (v***_in_/d***)—will be estimated using Microstructure Estimation Transformer with Sparse Coding (METSC) [47], a transformer-based architecture designed for multi-shell diffusion MRI. METSC addresses limitations of conventional non-linear optimization in biophysical multi-compartment models by learning latent representations directly from q-space samples. This approach reduces the number of diffusion encodings required, demonstrating reduced scan times while preserving or improving fitting accuracy.

TDD-derived microstructural metrics obtained using METSC will be evaluated for their ability to classify lesion categories and will contribute to the training and validation of the PROS-TD-AI framework.

### 2.7. Histopathologic Analysis

The interval between MRI examination and prostate biopsy will be limited to 30 days. All biopsy specimens will be interpreted by senior pathologists with over 10 years of experience, following the International Society of Urological Pathology (ISUP) grading standards [48]. The GSs of all tumor foci will be recorded and the findings grouped into five categories according to the ISUP grade groups (GGs): GS 3+3 (GG 1), GS 3+4 (GG 2), GS 4+3 (GG 3), GS 4+4 (GG 4), and GS over 4+4 (GG 5). For analysis purposes, benign lesions and PCa GG 1 will be classified as non-clinically significant prostate cancer (non-csPCa), while lesions within GGs 2–5 will be classified as csPCa. To link imaging findings to the reference standard, MRI-visible targets (index lesion and any additional PI-RADS ≥ 3 lesions) will be contoured and assigned standardized lesion identifiers and location labels. During MRI-guided biopsy, each targeted core will be recorded with the corresponding lesion identifier, enabling a core-level linkage between MRI targets and histopathology. When multiple targeted cores are obtained for a lesion (and when systematic cores are also available), the lesion-level classification will be determined using the highest ISUP grade group among the cores assigned to that MRI target, with predefined rules to adjudicate discordant or multifocal findings. Among csPCa cases, we will report the distribution of ISUP grade groups (1–5) and summarize lesion-level grade where applicable. Among non-csPCa participants, we will report alternative diagnoses, including benign histology and ISUP 1 (non-clinically significant cancer), and any other relevant findings (e.g., prostatitis/benign prostatic hyperplasia) when available.

### 2.8. PROS-TD-AI Output

PROS-TD-AI will provide a clinician-facing csPCa risk score (0–1) at the patient level and, when applicable, at the lesion level for PI-RADS 3–4 assessments. It will display prostate/lesion segmentation overlays and lesion probability maps co-registered with standard MRI sequences. Using prespecified, locked decision cutoffs (upgrade and downgrade cutoffs), it will recommend whether to maintain PI-RADS 3–4 or reclassify between PI-RADS 3 and 4 (3 → 4 or 4 → 3); however, these recommendations will not alter clinical management during this observational study.

### 2.9. Statistical Analysis

Microstructural parameters will be measured within manually delineated lesion ROIs, excluding boundary voxels to minimize partial-volume effects. In addition to mean values, we will compute a small prespecified set of alternative ROI summary statistics (e.g., median, selected percentiles, and dispersion metrics), with any feature-set selection performed strictly within the training data to avoid optimistic bias.

Post hoc comparisons among tissue categories (benign tissue and ISUP grade groups) will be performed using one-way ANOVA (or the Kruskal–Wallis test if assumptions are violated), followed by multiplicity-adjusted pairwise testing. Analyses will be conducted using RStudio (Version IDE 2026.01.0) and IBM SPSS Statistics (Version 31.0.1.0) software.

Diagnostic performance will be evaluated in the biopsy-verified PI-RADS 3–4 cohort (csPCa defined as ISUP ≥ 2). We will train and compare LDA, SVM, Random Forest, and XGBoost, selected to represent linear, margin-based, and ensemble tree-based approaches with different bias–variance trade-offs, using patient-level, stratified fivefold cross-validation with all pre-processing and hyperparameter tuning performed within training folds only. Model selection will be prespecified and specificity-driven. Among candidate classifiers, we will prioritize the approach that maximizes specificity for non-csPCa within the PI-RADS 3–4 cohort, while maintaining sensitivity above a prespecified minimum for csPCa. The upgrade and downgrade thresholds will be determined within training folds only using this prespecified criterion, then locked and applied unchanged to the held-out/prospective evaluation cohort. Performance will be reported with 95% confidence intervals.

PROS-TD-AI will output two continuous risk scores: an upgrade risk (0–1) for PI-RADS 3 cases (likelihood that the case should be managed as PI-RADS 4/csPCa-likely), and a downgrade risk (0–1) for PI-RADS 4 cases (likelihood that the case should be managed as PI-RADS 3/non-csPCa-likely). Prespecified, locked thresholds (the prespecified upgrade cutoff and the prespecified downgrade cutoff) will map these scores to a binary recommendation within the PI-RADS 3–4 decision zone (final recommendation: “3” vs. “4”), corresponding to non-csPCa-likely versus csPCa-likely classification in this subgroup.

The primary endpoint is the paired improvement in specificity (non-csPCa correctly recommended as “3”) of PROS-TD-AI-assisted recommendations versus standard PI-RADS (4 vs. 3), tested using McNemar’s test [49], in the non-csPCa subgroup (two-sided alpha = 0.01). The secondary endpoints include paired sensitivity in csPCa (McNemar), upgrade/downgrade reclassification rates stratified by pathology, and continuous-score discrimination (ROC AUC) and calibration (*p* < 0.05 for secondary analyses). We will present 2 × 2 cross-tabulations (index test vs. reference standard) for PI-RADS and PROS-TD-AI recommendations in the biopsy-verified PI-RADS 3–4 cohort, including counts of TP, FP, TN, and FN. Baseline demographic, clinical, and technical characteristics will be summarized for each analysis split (training/validation/test and the prospective evaluation cohort) to assess representativeness and potential distribution shift, including age, PSA/PSA density, prostate volume, PI-RADS category, and key acquisition variables (scanner/vendor and sequence quality markers). Because participants are consecutively enrolled within the routine intended-use pathway (biopsy-verified PI-RADS 3–4), we expect the csPCa prevalence to reflect this clinical setting. We will report the observed csPCa prevalence and discuss any material deviation as potential spectrum effects affecting generalizability.

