## Abstract

Prostate cancer (PCa) is the most common malignancy in men worldwide. Multiparametric MRI (mpMRI) improves the detection of clinically significant PCa (csPCa); however, it remains limited by false-positive findings and inter-observer variability. Time-dependent diffusion (TDD) MRI provides microstructural information that may enhance csPCa characterization beyond standard mpMRI. This prospective observational diagnostic accuracy study protocol describes the evaluation of PROS-TD-AI, an in-house developed AI workflow integrating TDD-derived metrics for zone-aware csPCa risk prediction. PROS-TD-AI will be compared with PI-RADS v2.1 in routine clinical imaging using MRI-targeted prostate biopsy as the reference standard.

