### 1.7. Deep Learning-Based Interpretation

Accurate lesion localization is essential because the peripheral and transition zones of the prostate differ markedly in architecture and cancer prevalence [30]. Advances in deep learning (DL) have enabled automated zone segmentation on both mpMRI and transrectal ultrasound, making zone-specific assessment feasible in routine practice [31,32].

Therefore, future work should evaluate zone-specific diagnostic performance of TDD-derived microstructural parameters and test machine learning algorithms for imaging-based PCa risk estimation, particularly given that reproducibility remains hampered by high inter-observer variability [33]. Within the standard diagnostic workflow, novel imaging techniques aim to reduce unnecessary biopsies by offering accurate and non-invasive detection of csPCa [34].

Accordingly, this study will prospectively assess the diagnostic contribution of TDD-derived imaging metrics integrated into an AI-based interpretation framework by comparing their performance in predicting csPCa against PI-RADS v2.1-driven mpMRI in real-world clinical practice. In line with this, the primary objective is to evaluate whether the AI-enhanced TDD-MRI pipeline (PROS-TD-AI) improves the classification of clinically significant prostate cancer (csPCa; ISUP grade group ≥ 2) within the PI-RADS 3–4 decision zone compared with standard PI-RADS v2.1 (with the primary endpoint being the paired specificity improvement for csPCa classification). The secondary objectives are as follows: (1) to develop and evaluate an automated prostate segmentation model (reporting the Dice similarity coefficient); (2) estimate TDD microstructural parameters and perform lesion/tissue classification (reporting AUC, accuracy, sensitivity, and specificity with 95% CIs); and (3) assess the integrated end-to-end PROS-TD-AI pipeline combining imaging and clinical features, including robustness and failure modes.

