## 4. Discussion

This protocol is designed to prospectively develop and evaluate novel imaging techniques and analytic approaches aimed at improving non-invasive detection of csPCa. By integrating time-dependent diffusion MRI (TDD-MRI) with AI-based quantitative analysis, this study seeks to enhance diagnostic specificity, reduce the reliance on invasive biopsy procedures, and provide accurate, low-risk, and more accessible risk stratification for men at intermediate clinical risk.

Demonstrating higher specificity and reliable performance of these novel imaging methods could have a significant impact on both research and clinical practice. Positive findings would provide a foundation for future randomized controlled trials and support evidence-based updates to current standard-of-care diagnostic workflows, potentially leading to more personalized and efficient patient management.

PROS-TD-AI may offer its greater incremental clinical value in diagnostic scenarios where mpMRI interpretation is most equivocal and PI-RADS exhibits lower specificity, particularly for PI-RADS 3–4 [51] lesions and transition-zone/central gland abnormalities, in which benign prostatic hyperplasia and stromal changes can closely mimic clinically significant disease [9]. In these settings, the addition of TDD-derived microstructural biomarkers and quantitative AI-based analysis may improve discrimination and reduce inter-reader variability, thereby refining risk stratification around biopsy decision thresholds and potentially decreasing unnecessary biopsies without compromising sensitivity for csPCa diagnosis.

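### The tissue comparison of microstructural parameters in section 2.9 has no zone term, so a peripheral/transition-zone difference can be mixed into the benign-versus-cancer difference

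*Protocol article*

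**What the plan says.** Section 2.9 fixes the test for the microstructural parameters: "Post hoc comparisons among tissue categories (benign tissue and ISUP grade groups) will be performed using one-way ANOVA". If the assumptions fail, Kruskal–Wallis replaces it. Pairwise tests with multiplicity adjustment follow. Tissue category is the only factor named.

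Section 1.7 gives the background: "the peripheral and transition zones of the prostate differ markedly in architecture and cancer prevalence". It adds that "future work should evaluate zone-specific diagnostic performance of TDD-derived microstructural parameters". The Abstract presents PROS-TD-AI as "an in-house developed AI workflow integrating TDD-derived metrics for zone-aware csPCa risk prediction".

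Zone does appear elsewhere:
- Sections 2.1 and 2.5 plan automatic zonal segmentation.
- Section 2.7 gives each MRI target a location label.
- Section 2.5.4 promises performance results by subgroup, with peripheral versus transition zone as an example.

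The article does not say whether zone is an input to the classifier.

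**The concern.** A variable confounds a comparison of tissue categories when it is related both to the category and to the measurement. The article states both links. Cancer prevalence differs by zone, so zone mix can be expected to differ between benign lesions and the grade groups. Architecture also differs by zone, and architecture is what intracellular volume fraction, cell diameter and extracellular diffusivity are meant to capture.

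A one-factor test cannot separate the two sources. Part of an apparent benign-versus-cancer difference could be a zone difference, or a real tissue difference could be hidden by one. The multiplicity adjustment does not help, because it controls the number of tests and not the bias within each.

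At stake is the interpretation of the parameters as markers of grade, which is the biological argument for the added sequence. The primary endpoint is not at stake.

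**Working it through.** **The plan's own figures, to show that they are untouched (section 2.10)**
- Non-csPCa participants: (2.576 + 0.842)² × 0.20 / 0.10² = 233.6, rounded up to 234.
- Total: 234 / 0.62 = 377.4, rounded up to 378.
- Inflation: 378 / 0.90 = 420 and 378 / 0.85 = 444.7, rounded up to 445.

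All match the article. The McNemar test compares two classifications of the same participant, so zone cannot confound it.

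**Bias in the tissue contrast**

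Let δ be the difference in a parameter between zones, in within-zone SD units, and let π_b and π_c be the peripheral-zone shares among benign and cancer lesions. With no true tissue effect within zone, the expected pooled difference is

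bias = δ × (π_c − π_b).

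The article gives neither δ nor the shares, so the values below are assumptions.
- Shares 50% and 75%: (0.75 − 0.50) × 0.5 = 0.125 SD; (0.75 − 0.50) × 1.0 = 0.25 SD.
- Shares 60% and 75%: (0.75 − 0.60) × 0.5 = 0.075 SD; (0.75 − 0.60) × 1.0 = 0.15 SD.
- Equal shares, or δ = 0: no bias.

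Reversing the sign of δ reverses the sign of the bias.

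**Effect on the test**

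Simulation settings: 378 lesions, one per participant, split 62% non-csPCa and 38% csPCa (the prevalence in section 2.10); normal data; no true tissue effect within zone; test level 0.05; 4,000 runs per setting. The grade groups are collapsed to two categories for simplicity.

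| Peripheral share, non-csPCa / csPCa | Zone shift (SD) | One-way ANOVA, false-positive rate | With zone as a factor |
|---|---|---|---|
| 60% / 75% | 0.25 | 7.1% | 4.8% |
| 60% / 75% | 0.5 | 9.9% | 4.3% |
| 60% / 75% | 1.0 | 25.7% | 4.6% |
| 50% / 75% | 0.25 | 8.8% | 5.4% |
| 50% / 75% | 0.5 | 20.5% | 4.8% |
| 50% / 75% | 1.0 | 56.9% | 5.9% |

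With equal shares (70% / 70%) or no zone shift, the one-way test stays between 4.4% and 5.4%. The inflation therefore comes only from the combination of unequal zone mix and a zone shift, and adding zone to the model removes it.

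**The case against.** The strongest reply is that the affected analysis is minor. Section 2.9 itself labels these comparisons post hoc, they are not among the listed primary or secondary endpoints, and secondary objective 2 is judged by AUC, accuracy, sensitivity and specificity. This stands and limits the weight of the point. A second reply is that a second factor cannot simply be added to Kruskal–Wallis. This also stands, and the fix must name a replacement.

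A reader might infer more: that the single pair of upgrade and downgrade cutoffs also confounds zone with pathology. The document does not support this.
- Section 2.9 says of the cutoffs: "Prespecified, locked thresholds (the prespecified upgrade cutoff and the prespecified downgrade cutoff) will map these scores to a binary recommendation". It does not say that the scores ignore zone. A common cutoff on a risk score that already uses zone is not confounded.
- No statement excludes zone from the classifier. The Abstract, the zonal segmentation in sections 2.1 and 2.5 and the use of anatomical information in section 3.2 point towards including it. A condensed article may leave the feature list to the full protocol.
- It would be too strong to say that zone-awareness goes unexamined, because section 2.5.4 promises performance by zone.
- One might expect a common cutoff to give the lowest specificity in the transition zone, because the Discussion says that "benign prostatic hyperplasia and stromal changes can closely mimic clinically significant disease". That sentence concerns conventional mpMRI reading and not the TDD parameters. Even for a score that ignores zone, the direction depends on the assumed shift. If benign peripheral lesions score 0.5 SD higher, 60% of the lesions are peripheral and pooled specificity is 0.70, specificity is 0.63 in the peripheral zone and 0.80 in the transition zone. The opposite shift favours the peripheral zone.

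**Conclusion.** The point holds for the tissue comparisons in section 2.9. A one-factor test is fixed for a contrast that, on the premise of section 1.7, zone can confound. The article gives no zone mix or zone shift, so neither the size nor the direction of the bias is known. Under the assumed 25-point difference in mix and a shift of 0.5–1.0 SD, it is 0.13–0.25 SD. It vanishes if either the mix or the parameter is the same in both zones.

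For the classifier and its cutoffs there is no shown error, only an input that the text leaves open. The primary comparison, its alpha, power and sample size stand. This is a modest point about a post hoc analysis, worth making because the remedy costs almost nothing.

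**What to change.** In section 2.9:
1. Add lesion zone (peripheral or transition) as a second factor in the ANOVA.
2. Replace the non-parametric fallback with a zone-stratified rank method, for example the van Elteren test for the pairwise comparisons, or Kruskal–Wallis within each zone.
3. Include zone among the candidate classifier inputs. Section 2.11 locks the final model before prospective enrollment, so this must be settled before that lock.

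Keep the zone-stratified performance reporting of section 2.5.4 as it is.

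The cost is one extra model term in a post hoc analysis and a few words of text. Zone is already available from the location labels and the zonal segmentation. No new data, sample-size change or change to the primary analysis is needed.
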